### Protocol adherance

The study supervisor monitors protocol adherence through multiple methods. First, they review video recordings of all sessions. Second, they hold supervision meetings with the therapist every two weeks. Third, they complete standardized fidelity assessments after each session.

For MBCT-C sessions, the supervisor uses the validated MBCT-C Adherence Scale. This tool measures how closely the therapist follows the established protocol. For LST sessions, the supervisor uses the Life Skills Training Fidelity Monitoring Checklist developed by Botvin and colleagues. Both assessment tools evaluate content delivery, participant engagement, and implementation of core techniques.

The supervisor provides feedback to facilitators immediately after reviewing each session. This allows facilitators to address any protocol deviations quickly. Such close monitoring ensures consistent program delivery across all four cohorts of participants.

### Measures

#### Mindful attention awareness scale**-**children (MAAS-C)

This unpublished self-report tool consists of 15 items to measure mindfulness in children (61). Participants will respond to the questions using a Likert scale ranging from 1 (*almost never*) to 6 (*almost always*). All 15 items are phrased negatively and reversely scored. This scoring approach means individuals receiving elevated scores demonstrate stronger mindfulness capabilities. The original MAAS-C has a good internal consistency among children (*α* = .84) (62).

#### State-trait anxiety inventory for children (STAI-Ch)

The STAI-CH is a self-report measure of anxiety levels in children (63). Two independent scales of this inventory are state anxiety (S anxiety) and trait anxiety (T anxiety). S anxiety assesses anxiety as a temporary emotional condition, and T anxiety evaluates anxiety as a trait of personality. Both scales consist of 20 items, each rated on a 3-point Likert scale from 1 (*rarely*) to 3 (*often*). The overall score for each variable ranges from 20 to 60. The State-Trait Anxiety Inventory for Children (STAI-CH) has exhibited strong psychometric properties. The internal consistency coefficients for both scales surpassed.80 (63). In addition, it has been shown that the psychometric properties of the Persian version of STAI-CH have good levels of internal consistency (*α* = .89) (64).

#### Emotion regulation checklist (ERC)

ERC is a commonly employed other-report (e.g., completed by parents or teachers) utilized to evaluate the emotion regulation capacities of children and adolescents (65). ERC includes 24 items scored on a 4-point Likert scale, from 1 (*never*) to 4 (*almost always*). Items are categorized into two subscales, Lability/Negativity and Emotion Regulation. Lability/Negativity evaluates how individuals encounter negative emotions and exhibit emotional instability. Emotion Regulation evaluates the capacity to regulate emotional reactions and engage in self-soothing actions. Numerous research investigations showed the ERC's robust psychometric characteristics. The internal consistency of ERC has been determined to be satisfactory for the Lability/Negativity (*α* = .96) and the Emotion Regulation subscale (*α* = .83). The ERC exhibits strong convergent validity when compared to other assessments of behavioral problems and social skills (66). The capacity to detect changes has also been evidenced in intervention studies, wherein enhancements in the aptitude to regulate emotions were correlated with a reduction in negative emotional states and an elevation in positive emotional states. The present study will use the Persian version of the ERC. This checklist has high internal consistency (*α* = .90) in an Iranian population and has convergent validity and acceptable discriminant validity (67).

#### Attentional control scale for children (ACS-C)

ACS-C is a 20-item self-report scale (68) to assessing attentional control among children. Each item is rated on a five-point Likert scale that ranges from 1 (*almost never*) to 4 (*always*). Items evaluate three distinct aspects of attentional control: focusing, shifting, and flexibility. The internal consistency of ACS-C has been reported to be good in different studies [*α* = .78 and .74 (69, 70)]. The present research will utilize the Persian adaptation of the ACS-C. As this version has not yet been standardized for use in Iran, the internal consistency of the questionnaire will be evaluated during the study's second phase.

### Satisfaction and adherence measures

#### Mindfulness program satisfaction questionnaire (MPSQ)

MPSQ was developed by Semple (2016) using the items of the original version of the Client Satisfaction Questionnaire [CSQ (71)]. It includes 8 items rated on a 4-point Likert scale. Half of the items are scored directly (including 5, 4, 2, and 8), and the other half is scored in reverse (1, 3, 6, and 7). Scores range from 8 to 32, and higher scores indicate higher satisfaction with the MBCT-C program.

#### Life skills training satisfaction questionnaire (LSTSQ)

We will use an adapted version of the Client Satisfaction Questionnaire [CSQ-8 (71)] to measure participant satisfaction in the LST group. This adapted questionnaire maintains the original 8-item structure with a 4-point Likert scale, with modifications to reflect LST-specific content. Scores range from 8 to 32, with higher scores indicating greater satisfaction with the LST program.

### Ethical standards

We registered the present study in the Iranian Registry of Clinical Trials (IRCT; IRCT20230922059488N1). We will follow the ethical guidelines related to human experiments. In addition, we will adhere to the principles outlined in the Declaration of Helsinki in 1975, which was subsequently revised in 2008, in all study phases. Given that the research will be conducted with children under age 18, a formal informed consent document must be signed by a guardian or parent of everyone included in the study. Children will provide verbal assent to participate. Participants may discontinue the intervention at any point during the research voluntarily.

Participant anonymity will be maintained through the assignment of unique identification codes in place of personal information. Names and contact details will be replaced with pseudonyms during data collection. Each participant will receive a distinct identifier that will prevent direct linkage to individual identities. The coding key will be stored separately from the main dataset in a secure location. Data storage will follow standard security protocols. An encrypted database will house all collected information, with access restricted to designated research team members.

The research director, ethics committee, and IRCT will be duly informed of any probable modifications made to the study, and these changes will be subsequently documented in the IRCT. This study protocol received approval from the local ethics council at the Azad University- North Tehran Branch (ethics code: IR.IAU.TNB.REC.1402.067).

### Statistical strategy

The study results will adhere to the guidelines established by the SPIRIT guidelines (72). The analysis will be conducted using the STATA-18 software. After data collection and curation, to determine data consistency, we assess the status of outliers by calculating both the average and a 5% reduced average (*p* < .05). We shall also analyze demographic differences in the baseline utilizing independent *t*-tests and chi-square tests. Furthermore, an intention-to-treat (ITT) analysis will be conducted should any participant miss more than three intervention sessions. This approach ensures that missing data does not significantly bias the study's primary analysis, remaining below 5% of the total data. In such instances, multiple imputations will replace missing values with alternative ones.

To evaluate the study outcomes, we will use a conditional mixed regression model to simultaneously compare the fixed and random effects of two groups (MBCT-C vs. LST) at the three assessment times (T1, T2, T3). The fixed effects will include group, time, and the group-by-time interaction, enabling the assessment of changes in the main outcomes across time and between groups. Participant ID will be treated as a random effect to account for repeated measurements within individuals. Where appropriate, baseline variables such as age and gender will be included as additional fixed effects to examine their potential role in moderating intervention outcomes. All analyses in the present study will evaluate the results at a significant level (*p* < .05). The Reliable Change Index (73) will be applied to examine clinically significant changes in primary and secondary outcomes before and after MBCT-C. A statistically significant difference will be represented by an RCI greater than 1.96.

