Children's clinical intervention programs should not be limited to clinical populations; their prophylactic effectiveness should also be examined in non-clinical populations. These programs may have significant benefits in preventing childhood problems (54). The primary aim of the present study protocol is to outline the theoretical framework and methodology of a quasi-experimental study to investigate the effectiveness of MBCT-C in managing non-clinical anxiety, emotion regulation, and attentional control in children. Five hypotheses are proposed:

Primary hypothesis
1.Following a 12-session MBCT-C program, children in this group will report significantly increased mindfulness compared to children attending a 12-session Life Skills Training (LST) program, as measured by the Mindful Attention Awareness Scale for Children (MAAS-C).Secondary hypotheses
2.Following a 12-session MBCT-C program, children in this group will report the MBCT-C group will report significant decreases in state and trait anxiety as compared to children attending a 12-session LST program, as measured by the State-Trait Anxiety Inventory for Children (STAI-CH).3.Following a 12-session MBCT-C program, children in this group will report a significant increase in emotion regulation as compared to children attending a 12-session LST program, as measured by the Emotion Regulation Checklist (ERC).4.Following a 12-session MBCT-C program, participants in this cohort will report a significant increase in attentional control when compared to children participating in a 12-session LST program, as measured by the Attention Control Scale for Children (ACS-C).5.The MBCT-C program will be acceptable to children and their parents as measured by recruitment, attendance, drop-out rates, and the Mindfulness Program Satisfaction Questionnaire (MPSQ).

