## Method

### Study design

This is a quasi-experimental study that comparing an MBCT-C program to an active control groupthe. Demographic data will be collected at baseline. Assessment data will be collected at baseline (T1), post-intervention (T2), and 6-month follow-up (T3) (Figure 1). Participants will be randomly assigned to either MBCT-C or LST using a software-generated random sequence. A stratified block randomization method will ensure balanced distribution by gender and age. A comparison of attendance and drop-out rates between the MBCT-C and LST groups will be one marker of program acceptability. Participants' adherence to the intervention will be evaluated via session attendance, group activity participation, and homework assignment compliance. To reduce potential bias, assessors will be blind to group allocation.

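### The outcome model treats the T1 score as an outcome with a free group effect, so the T2 comparison is a change-score contrast: unbiased, but less precise than adjusting for baseline

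*Protocol article*

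**What the plan says.** The Study design section sets three assessments: "Assessment data will be collected at baseline (T1), post-intervention (T2), and 6-month follow-up (T3"). The Statistical strategy section compares "two groups (MBCT-C vs. LST) at the three assessment times (T1, T2, T3") in one mixed model. Its mean structure is given as "The fixed effects will include group, time, and the group-by-time interaction", and its within-child structure as "Participant ID will be treated as a random effect to account for repeated measurements within individuals".

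On covariates the section says: "Where appropriate, baseline variables such as age and gender will be included as additional fixed effects". It presents these as possible moderators. The T1 score of the outcome scale is not among the examples. The model is called conditional, but the article does not say on what.

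The primary hypothesis in the Introduction reads: "Following a 12-session MBCT-C program, children in this group will report significantly increased mindfulness", in comparison with the LST children, on the MAAS-C. Neither section says which coefficient of the model decides it.

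**The concern.** Children are allocated at random in a 1:1 ratio, so the true T1 means of the two arms are equal and any observed T1 difference is chance. A model that gives T1 its own group effect estimates that chance difference and, in the group-by-T2 term, subtracts it in full. Baseline adjustment subtracts only the part that predicts the T2 score.

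What is at stake is precision, not validity. The Sample size section accepts that the sample limits detection of smaller effects, and the Discussion says a larger sample was not feasible. Precision that can be had from T1 scores already being collected therefore matters here.

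**Working it through.** **Inputs from the article.** Two groups, 1:1; alpha .05; effect size .5; minimum of 64 participants, so 32 per arm. Enrolling 80 and losing 20% also leaves 80 × 0.8 = 64.

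**Assumptions.** The effect size is read as a standardised mean difference (the article does not name the metric). The test is two-sided, the variance is equal at each time and set to 1, and data are complete. The T1–T2 correlation rho is not given, so a range is shown. The plan states no figure for this contrast, so there is none to reproduce.

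**Step 1: what the T2 coefficient is.** With categorical time, the group coefficient is the T1 difference between arms and the group-by-T2 coefficient is (T2 difference) − (T1 difference), which is the difference in mean change. One simulated complete data set (40 per arm, participant random intercept) confirmed this: fitted group-by-T2 coefficient 0.69667, raw difference in T2–T1 change 0.69667.

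**Step 2: variance per child.**
- Change score: 2(1 − rho)
- Adjusted for T1: 1 − rho²
- Ratio, adjusted to change score: (1 − rho²) / [2(1 − rho)] = (1 + rho)/2

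The ratio is below 1 for every rho below 1. When rho is below .5, 2(1 − rho) exceeds 1, so the change-score contrast is then less precise than comparing T2 scores and ignoring T1. In a check at rho .3, .5, .6 and .7 with equal correlations, a model constrained to equal T1 means gave the same standard error as covariate adjustment.

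**Step 3: power.** With v the per-child variance, SE = √(2v/32) and noncentrality = 0.5/SE, using the noncentral t.

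| rho | v change | v adjusted | ratio | SE change | SE adjusted | power change | power adjusted |
|---|---|---|---|---|---|---|---|
| .3 | 1.40 | 0.91 | 0.65 | 0.296 | 0.238 | 38% | 54% |
| .5 | 1.00 | 0.75 | 0.75 | 0.250 | 0.217 | 50% | 62% |
| .7 | 0.60 | 0.51 | 0.85 | 0.194 | 0.179 | 72% | 79% |

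With all 80 children analysed (40 per arm) the pairs are 46% and 64%, 60% and 72%, 81% and 87%. At rho .9 the variance ratio is 0.95 and little is left to gain.

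**Step 4: within-child covariance, conditional on a reading.** Suppose the participant effect is a lone random intercept with independent, equal-variance residuals. The model then uses one correlation, about the average of the three. For each change contrast the model variance is 2(1 − average) and the true variance is 2(1 − own correlation). The approximate type I error is 2Φ(−1.96 √[model variance / true variance]).
- Assumed T1–T2, T1–T3, T2–T3 = .7, .5, .6: average .6, model variance 0.8, true 0.6 at T2 and 1.0 at T3. Type I error is about 2.4% at T2 and 8.0% at T3.
- Assumed .5, .5, .7: average .567, model variance 0.867, true 1.0 at both. Type I error is about 6.8% at T2 and at T3.

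The T2 error moves in opposite directions in the two cases.

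**The case against.** The strongest reply is that a group-by-time mixed model is a standard, unbiased analysis, that it matches a hypothesis about relative increase, and that the benefit of adjustment depends on an unknown correlation. All of that stands, and it limits the point to efficiency. It can be added that the model is called conditional and that the covariate list is open, so a baseline score is not excluded. But the listed terms do not describe conditioning on the T1 score, and adding T1 as a covariate while T1 also stays in the outcome would not be the adjusted analysis described here.

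A reader might go further in three ways that the article does not support.
- **That the model cannot isolate the T2 effect, or that a joint 2-df interaction test is planned.** With categorical time the T2 contrast is already a 1-df coefficient, and no joint test is announced. The fair statement is that the article does not say which coefficient is primary. A fuller plan may do so.
- **That a random intercept only is specified, forcing equal correlations.** The article says participant ID is a random effect. It does not say that nothing else is, and it is silent on residual covariance, which an article commonly leaves to the full plan.
- **That T2 standard errors will be too large and T3 standard errors too small.** The article gives no correlations, and the second case in Step 4 reverses the T2 direction.

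**Conclusion.** The point holds as a loss of efficiency, not as bias. On the terms listed, the T2 effect is a change-score contrast whose variance is 2/(1+rho) times that of a baseline-adjusted estimate: 1.54 at rho .3, 1.33 at .5, 1.18 at .7. At 32 analysed per arm this is about 16, 12 and 7 power points. The equivalence assumes categorical time and complete data. The power figures also assume a standardised difference of 0.5, equal variances and the rho values shown, and the gain fades towards zero as rho approaches 1.

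T2 as the primary time point is an inference, though the natural one: the hypothesis speaks of mindfulness following the programme, and T2 is the post-intervention assessment. The covariance question is conditional and its direction cannot be known in advance, so it supports a recommendation but is not an error in the plan.

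**What to change.** 1. Keep T1, T2 and T3 in one model but constrain the T1 means to be equal across groups; or model T2 and T3 only, with the T1 score of the same scale as a covariate. Treat time as categorical. Use the same form for the other scales measured at all three times.
2. Designate the MBCT-C minus LST difference in MAAS-C at T2 as the primary contrast, with the T3 difference secondary.
3. State the within-child covariance. Unstructured is sensible: with three visits it has 6 parameters against 2 for compound symmetry, so four more.
4. Say what the model is conditional on, or drop the word.

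The cost is wording. T1 is already scheduled for every child, and at the time of writing the interventions had not begun. No further recruitment or measurement is needed.

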### Sample size

According to Thibault & Pedder (55) and Treves et al. (56), the required sample size for this study to achieve sufficient statistical power was determined using G*Power software (57). In this calculation, we used *a priori* power analysis with the following parameters: significance level *α* = .05; effect size = .5 (58); power (1-*β*).95; with two groups, corresponding to the study design. A minimum of 64 participants was estimated to detect hypothesized effects reliably. Recognizing the possibility of participant attrition, we incorporated a buffer to protect the power of the study. Specifically, we estimated a dropout rate of 20%, increasing the sample by an additional 14 participants (calculated as 20% of 64, rounded). This adjustment resulted in a total sample size of 77 (rounded to 80) participants. However, we acknowledge that this sample size limits our ability to detect smaller effect sizes. We have adjusted our expectations accordingly, focusing on larger effects as suggested by prior research (e.g., Goldberg et al. (59), for mindfulness interventions on stress.

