### Recruitment and randomization procedures

In this study, our sampling framework encompasses four schools (two female-only and two male-only institutions) randomly selected from diverse districts across Tehran to ensure appropriate population representation. The target population comprises all middle school students in Tehran who, according to Iran's educational system, attend gender-segregated schools.

The necessary research permits will be obtained from Tehran's Education Department through the university's Research Vice-Chancellor's office. Group intervention sessions will be conducted after regular school hours in the counseling rooms of the participating schools, providing a quiet and appropriate environment for group therapeutic activities. This approach facilitates student access to the program while avoiding interference with their academic schedules.

Furthermore, school counselors will explain the research and introduce interested parents and students to the research team. Should these recruitment techniques be insufficient to obtain the desired sample size within a reasonable time, we will extend recruitment to additional schools within the Tehran education district.

Potential participants who contact the research assessment team will undergo an in-person screening to determine their eligibility. Inclusion criteria include: (a) primary school students, (b) age between 8 and 12 years old, (c) living in Tehran, and (d) ability to speak Persian. Exclusion criteria comprise (a) reporting an acute physical illness, (c) receiving psychotropic medications, and (e) receiving concurrent psychotherapy. Children who meet the criteria for this study and agree to participate will be enrolled with the consent of a parent or caregiver. Once the desired sample size is enrolled, participants will be randomized to the MBCT-C or LST group using online random allocation software (https://miniwebtool.com/de/number-randomizer/). The allocation will be made in a 1:1 ratio, ensuring equal representation of participants in each group.

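### Age and gender are to be added as plain fixed effects to examine moderation, which such terms cannot show, and inclusion of these two stratification factors is left open

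*Protocol article*

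**What the plan says.** All places are in the Method part of the protocol article.

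- **Study design** names the stratification factors: "A stratified block randomization method will ensure balanced distribution by gender and age".
- **Statistical strategy** sets the core of the mixed model: "The fixed effects will include group, time, and the group-by-time interaction". The only random effect is the child: "Participant ID will be treated as a random effect to account for repeated measurements within individuals".
- The same paragraph then deals with covariates: "Where appropriate, baseline variables such as age and gender will be included as additional fixed effects to examine their potential role in moderating" the outcomes of the intervention. The list of variables is open, the condition for including them is not defined, and no product with group is named.
- An earlier paragraph of that section announces tests of baseline balance: "We shall also analyze demographic differences in the baseline".
- **Recruitment and randomization procedures** describes the sampling frame as "four schools (two female-only and two male-only institutions".

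**The concern.** There are two faults in one sentence.

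First, the term does not match its purpose. A fixed effect for gender asks whether boys and girls differ in their average score. Moderation asks whether the MBCT-C versus LST difference is larger in one gender than in the other. Followed as written, the analysis could present an ordinary gender or age difference as a moderated treatment effect, and could miss moderation that is present.

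Second, the two factors used to stratify allocation are known before any outcome is seen, so nothing is gained by leaving their inclusion open. An undefined condition and an open list leave room to choose the covariates after the data are in.

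**Working it through.** **Inputs.** From the article: 80 children enrolled, 1:1 allocation, three assessments, participant as random effect, two-sided 5% level taken for the calculations. 80 less the stated 20% dropout is 64. Assumed, because the article gives no values: outcome SD 1 apart from stratum effects, within-child correlation 0.5, two equal strata per factor, complete data. The simulations fitted the random-intercept model by REML, 600 runs per scenario.

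The point rests on no figure in the plan; 64 and 80 serve only as sample sizes. (With d = 0.5, 95% power and a two-sided 5% test, two means need 105 per arm. The stated inputs, read that way, do not reproduce 64. That is a separate matter.)

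**1. What the additive term estimates.** Write the model as

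y = b0 + b1·group + b2·time + b3·group×time + c·gender + child + error.

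The intervention effect on change is b3 for boys and b3 for girls. Their difference is zero by construction, whatever c is. Moderation would be the coefficient of group×time×gender, which is not in the model.

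**2. How the gender term behaves.** The mean of three assessments has variance (1 + 2×0.5)/3 = 0.667, so the SE of c is √(4/80 × 0.667) = 0.183.

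- *No moderation, 0.8 SD gender difference:* 0.8/0.183 = 4.38; power Φ(4.38 − 1.96) = 0.99. Simulated: 0.988 to 0.997.
- *Moderation 1.0 SD, no baseline gap:* if present in the MBCT-C arm at T2 and T3, it adds 1.0 × 1/2 × 2/3 = 0.33 to the average gender difference. 0.33/0.183 = 1.83; power Φ(1.83 − 1.96) = 0.45. Simulated: 0.42.
- *Moderation 1.0 SD, baseline gap of −0.33 SD:* the two cancel. Simulated: 0.04.

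The last two cases have the same moderation; only the baseline gap differs. The three-way term was significant in 0.615 and 0.633 of those runs.

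**3. Power of a proper moderation test.** A difference in effect between two equal strata compares four cells of N/4, so SE = √(16/N).

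| N | SE | Power for 0.5 SD | Detectable at 80% power |
|---|---|---|---|
| 80 | 0.447 | Φ(1.118 − 1.96) = 0.20 | (1.96 + 0.842) × 0.447 = 1.25 SD |
| 64 | 0.500 | Φ(1.000 − 1.96) = 0.17 | (1.96 + 0.842) × 0.500 = 1.40 SD |

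This is for one time point. At correlation 0.5 the change from baseline also has SD √(2 × 0.5) = 1, so the figures carry over to change.

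**4. What inclusion does to the treatment test.** A child's gender and age band are constant over time, so their main effects cancel from within-child change. In the simulations the group-by-time estimate was the same with and without them (difference 0.0, SE ratio 1.000). Type I error was 0.048 either way, and power at 0.5 SD was 0.603 either way.

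A group comparison at a single time point is different. If each factor shifts the outcome by b SD, leaving both out multiplies the estimated SE by √(1 + b²/2), although stratification has already balanced them. Results from 20,000 runs per case:

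| b (assumed) | SE factor | Type I error, omitted | Power at d = 0.5, omitted | Power, included |
|---|---|---|---|---|
| 0.3 | 1.02 | 0.043 | 0.58 | 0.60 |
| 0.5 | 1.06 | 0.038 | 0.55 | 0.60 |
| 0.8 | 1.15 | 0.025 | 0.48 | 0.60 |

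Omission is therefore conservative and costs power.

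**The case against.** The strongest reply is that the article's own use of fixed effects covers interactions, since group-by-time is listed among them. The authors may have intended product terms and left their exact form to a fuller plan. Moderation is also not among the five hypotheses, and the group-by-time test barely depends on the outcome of this argument.

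The last two points stand and limit the weight of the concern. The first does not remove it. The sentence enters the baseline variables themselves, and where the article means an interaction it says so. A reader who carries out what is written fits additive terms and reads them as moderation. That is a wrong statement in the text and not a detail deferred.

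It is also fair to say that age and gender are at least named as candidate covariates. What is missing is the commitment to include them.

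**Conclusion.** The point holds in two parts. The additive terms cannot answer the moderation question they are assigned to, and inclusion of the stratification factors is not fixed. The first follows from the form of the model. The rates of 99%, and of 4% to 42%, rest on the assumed gender differences, the assumed 1.0 SD moderation, correlation 0.5 and complete data. The second has almost no effect on the group-by-time test and matters for group comparisons at one time point, by the amounts shown. With dropout the equality in step 4 is only approximate. The sentence should be changed before analysis, but it does not threaten the main comparison.

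A reader might infer more, and the documents do not support it:

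- *That stratification is ignored in the analysis.* The factors are named and may be included; adjustment is merely not guaranteed.
- *That the SE of the treatment effect is inflated by about 5%.* That is 1/√0.9 = 1.054, for an assumed 10% of variance explained. It applies to a single time point, not to the group-by-time term.
- *That baseline tests choose the covariates.* The two sentences stand in different paragraphs and neither refers to the other. A 23% chance of a false alarm (1 − 0.95⁵) also needs five independent tests, and the article gives no number of tests.
- *That school or cohort is an allocation factor carrying gender.* Only gender and age are named as stratification factors, and the cohorts of 20 are nowhere said to be single-sex.

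**What to change.** In Statistical strategy, replace the covariate sentence with two statements.

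1. Age and gender, as randomisation factors, enter every outcome model regardless of any baseline test.
2. Moderation is examined in a separate exploratory model with group-by-time-by-age and group-by-time-by-gender terms and their lower-order terms, reported as estimates with confidence intervals. The text should say that power is low, citing the figures in step 3. It should also say that gender cannot be separated from school: every school is single-sex, so a boy–girl difference in effect is also a difference between sets of schools.

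The cost is a few extra parameters and a plainly exploratory label on the moderation results. No new data are needed. The Result section describes screening as under way and the interventions as not yet begun, so at that stage the wording can be changed before any outcome is seen.
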